6.2. Adverse event report

The doctor in charge of each facility promptly notifies the data center of the serious adverse event emergency report promptly when admitting the evaluation target adverse event (serious adverse event which is not denied the relation with the examination) FAX transmission is performed. The data center regularly reports on the occurrence of the adverse event to be evaluated to the research representative. The research representative shares information with the research group and the test execution facility about the occurrence of the adverse event to be evaluated.

6.2.1. Reporting to the Independent Data Monitoring Committee

(1) The research representative shall periodically report to the Independent Data Monitoring Committee on the adverse event to be evaluated reported from each facility, and at the same time, appropriately reflect the viewpoint of the research representative for the adverse event and the response to the adverse event Ask for examination on sex.

(2) The Independent Data Monitoring Committee reviews the content of the report and recommends to the research delegate in writing the future response including handling of cases and whether to continue the registration.

7. Data collection

7.1. Case report form (CRF)

7.1.1. Data submission

In this study, case registration forms and other case report data are submitted by FAX. The doctor in charge or the clinical research coordinator (CRC) etc. will submit data using FAX to the data center according to the progress of the examination, for all cases registered in this examination until the examination is completed. In the case where CRC or the like fills in or inputs, confirmation by the attending physician is obtained. The contents of the data to be submitted, the means of submission and the submission date are shown below.

7.1.2. Case report type and submission deadline

The types of CRF used in this study, the means and timing of sending and submitting are shown below.

| No. | Type | Means of sending to facilities, timing | Means of submission |
| --- | --- | --- | --- |
| 1 | Case registration card | - Mailing - Immediately after registering facilities | - FAX transmission - At the time of registration |
| 2 | Case registration card | - Mailing - Immediately after registering facilities | - FAX transmission - Within one month from each survey |
| 3 | Serious adverse event emergency report | - The doctor can also use the each-hospital format - Mail in advance to participating facilities | - FAX transmission - Immediately after knowing the occurrence of an emergency reporting adverse event |

7.1.3. Data management

In accordance with a separately specified data management plan (standard operating procedure and manual), the data center performs dunning of data not submitted, scrutiny and inquiries of the submitted data, data correction based on the inquiry result, database management. In addition, the data center prepares data for monitoring and data set for statistical analysis.

8. Endpoint

8.1. Endpoint definition

8.1.1. Primary endpoint

Develop algorithms to calculate indices of hepatic fibrosis, inflammation, fatty liver using RTE, SWM, and attenuation measurement

8.1.2. Secondary points (Secondary Evaluation Item)

- Relationship between indicators calculated using RTE, SWM, attenuation measurement and blood test results.
- Relationship between indicators calculated using RTE, SWM, attenuation measurement and pathological diagnosis.
- Correlation between indicators calculated using RTE, SWM, attenuation measurement and other elastography and attenuation measurements.

9. Statistical matters

9.1. Definition of analysis target group

The group to be analyzed used for periodic monitoring, intermediate analysis, and final analysis is defined as follows.

(1) All registration example: All patients registered in accordance with the registration procedure are "all registered examples".

(2) Ineligible Example: Among registered patients, patients who do not satisfy the registration criteria (the fact that they do not agree with each other later) are referred to as "ineligible cases".

(3) All qualified examples: The group excluding "incapacitated cases properly decided in the research group" from all registered examples shall be regarded as "all qualified examples".

9.2. Analysis of Primary endpoint

Regarding the association between pathological diagnosis and RTE / SWM / attenuation measurement, index of liver fibrosis, inflammation, fatty liver is calculated using multiple regression analysis and data mining etc. Also, sub-analysis is performed for each disease and examined.

9.3. Analysis of Secondary endpoints

Pearson correlation coefficients and so on are evaluated to evaluate the association between the indicators of hepatic fibrosis, inflammation and fattying by each elastography and attenuation measurement and serum markers, respectively.

Pearson correlation coefficients and so on are evaluated in order to evaluate the relevance between the indicators of hepatic fibrosis, inflammation and fattying by each elastography and attenuation measurement and the pathological diagnosis.

Pearson correlation coefficients and so on are evaluated to evaluate correlations between liver fibrosis, inflammation, fatty index and other elastography and attenuation measurements by each elastography and attenuation measurement, respectively.

Also, sub-analysis is performed for each disease and examined.

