0.2. Purpose

We perform Real-time Tissue Elastography (RTE), Shear Wave Measurement (SWM) and attenuation measurement on liver disease patients who undergo liver biopsy or liver resection. We develop an algorithm to estimate indices of liver fibrosis, liver inflammation, liver steatosis by these modality.

At the same time, these indicators and liver tissue diagnosis, blood test, or other elastography (FibroScan, Virtual Touch Quantification (VTQ), ShearWave Elastography (SWE), Shear wave with Smart maps (SwSm), Shear Wave Elastography (SWE_GE) MR Touch) are compared. Investigate whether we can evaluate the general condition of the liver non-invasively such as liver fibrosis, liver inflammation, and liver steatosis.

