5.2.1 Blood test

5.2.1. Blood test

Of the following tests, those underlined ( ) do blood test on an empty stomach.

Biochemistry: AST, ALT, γGTP, ALP, total bilirubin, direct bilirubin, total protein, albumin, protein fraction, cholinesterase, total cholesterol, LDL cholesterol, HDL cholesterol, triglyceride, BUN, Cr, plasma glucose, HbA1c, insulin, ferritin, serum Fe, TIBC, UIBC.

Blood cell: white blood cell count, red blood cell count, hemoglobin, hematocrit, number of platelets.

Coagulation: prothrombin time (%, INR).

Fibrotic marker: hyaluronic acid, type IV collagen 7S, procollagen III peptide (P-Ⅲ-P), M2BPGi.

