5.2.2. Liver pathology

- Liver biopsy or liver resection pathology specimens are stained with ① HE staining and ② masson trichrome staining.
- Make the slide virtual slide and send it to independent pathology interpretation committee member.
- Independent pathology interpretation committee evaluates fibrosis in accordance with new inuyama classification (complies with METAVIR classification).

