5.2.6. Vibration-Controlled Transient Elastography (VCTE)

- For facilities owned by FibroScan, evaluation is also performed with Vibration-Controlled Transient Elastography within 4 months before and after liver fibrosis evaluation by liver biopsy, hepatectomy, RTE, or SWM.
- Transducer: M-probe, XL-probe
- Inspection 10 times at the right intercostal space, validity of 60% or more is recognized, and when the IQR is less than 1/3 of the measured value, the examination is judged as valid.

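### Section 9.3 names only Pearson's r for relating the indices to pathology, which does not measure how well an index separates ordered fibrosis stages

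*Protocol*

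**What the plan says.** Protocol 9.3 uses the same formula three times: for serum markers ("Pearson correlation coefficients and so on are evaluated to evaluate the association between the indicators of hepatic fibrosis, inflammation and fattying"), for pathology ("Pearson correlation coefficients and so on are evaluated in order to evaluate the relevance") and for other elastography and attenuation measurements. The only step on case mix is a sub-analysis by disease.

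The fibrosis reference is set in 5.2.2: "Independent pathology interpretation committee evaluates fibrosis in accordance with new inuyama classification (complies with METAVIR classification". No scale is given there for inflammation or steatosis. The serum fibrosis markers are listed in 5.2.1 ("Fibrotic marker: hyaluronic acid, type IV collagen 7S, procollagen III peptide (P-Ⅲ-P), M2BPGi") with nothing on their distribution.

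The aim in 0.2 is wider than a correlation: "Investigate whether we can evaluate the general condition of the liver non-invasively such as liver fibrosis, liver inflammation, and liver steatosis". Section 9.4 sets aside 100 biopsy or resection cases and 20 healthy cases to check that the calculated indices are useful, but attaches no statistic to that check. The primary endpoint in 8.1.1, "Develop algorithms to calculate indices of hepatic fibrosis, inflammation, fatty liver using RTE, SWM, and attenuation measurement", has no performance measure either, and 9.2 names only fitting methods. The secondary endpoint against pathology is worded as a correlation in 0.3.2 and as a relationship in 8.1.2.

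Comparator devices are measured where they are available, for example in 5.2.6: "For facilities owned by FibroScan, evaluation is also performed".

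**The concern.** A fibrosis stage is an ordered class. Computing Pearson's r on stage codes treats the step between any two neighbouring stages as the same size. The result describes linear association in the sample at hand. It does not say how often the index ranks a patient with more advanced fibrosis above one with less, which is what a non-invasive substitute for biopsy has to do.

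r also changes when the spread of stages changes, even if the index behaves identically within each stage. The protocol sets no stage quotas and mixes biopsy cases, resection cases and healthy volunteers. A value from the verification set could therefore be high or low partly because of who was enrolled. No measure of stage separation appears in the protocol to set beside it.

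**Working it through.** **Plan's own figure.** The verification and teacher sets add up: (300 + 100) + (30 + 20) = 450, the target in 4.1.2. The protocol states no correlation, AUROC or precision target, so there is no further figure to reproduce.

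**Assumptions.** The protocol gives no stage distribution, stage means or noise. Five stages k = 0 to 4 are assumed, with index means m = 0, 0.15, 0.5, 1.1, 2.0 and normal noise σ = 0.8 (σ² = 0.64). These are held fixed and only the stage mix p changes:
- A: 10/30/25/20/15%
- B: 2/45/35/13/5%
- C: 30/10/10/15/35%

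**Pearson.** r = Cov(k, m) / √[Var(k) × (Var(m) + σ²)]
- A: 0.7750 / √(1.5000 × 1.0752) = 0.61
- B: 0.4017 / √(0.7924 × 0.8592) = 0.49
- C: 1.4105 / √(2.8275 × 1.3839) = 0.71

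**Pairwise-stage AUROC.** For stages i < j, A_ij = Φ[(m_j − m_i) / (σ√2)], which does not involve p. The ten values are 0.553, 0.671, 0.835, 0.961, 0.621, 0.799, 0.949, 0.702, 0.908 and 0.787. Their sum is 7.786, so the unweighted mean is 0.78 in all three mixes. It is constant by construction, because each term compares two stages only.

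**Other candidate measures under the same three mixes (A, B, C).**

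| Measure | A | B | C |
|---|---|---|---|
| Pearson | 0.61 | 0.49 | 0.71 |
| Spearman (simulated) | 0.60 | 0.43 | 0.74 |
| AUROC, stage ≥1 | 0.72 | 0.65 | 0.83 |
| AUROC, stage ≥2 | 0.77 | 0.70 | 0.88 |
| AUROC, stage ≥3 | 0.84 | 0.81 | 0.90 |
| AUROC, stage 4 | 0.90 | 0.91 | 0.91 |
| Pairwise mean, weights p_i p_j from the sample | 0.76 | 0.71 | 0.83 |
| Pairwise mean, equal weights | 0.78 | 0.78 | 0.78 |

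A threshold AUROC is Σ p_i p_j A_ij / [P(k < t) × P(k ≥ t)], summed over i < t ≤ j, so it inherits the mix. The last two rows show that the weights must be fixed in advance: weights taken from the sample bring the dependence back.

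**Does r reflect anything besides mix?** Take an even mix with equal mean steps d and within-stage SD 1. Then Var(k) = 2 and r = d√2 / √(2d² + 1). For d = 0.3, r = 0.424 / 1.086 = 0.39. For d = 1.0, r = 1.414 / 1.732 = 0.82. At d = 0.6, changing only the mix moves r over 0.51 to 0.73. So r follows true discrimination at least as much as it follows mix.

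**Healthy volunteers.** In the same d = 0.6 model, adding 20 healthy cases, taken as stage 0, to 100 cases concentrated in the middle stages raises r from 0.52 to 0.58. Adding them to an even mix raises it from 0.65 to 0.67.

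**Skew, if present.** Exponentiating the index in the even-mix model lowers Pearson from 0.65 to 0.40. Spearman stays at 0.65 and the AUROC for stage ≥2 at 0.84.

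**Sampling error for scale.** The Fisher interval for r = 0.7 at n = 120 is tanh(0.867 ± 1.96/√117) = 0.60 to 0.78. The span of 0.22 between mixes B and C (0.71 − 0.49) is wider than that interval.

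**The case against.** The strongest defence is that Pearson fits the endpoint as written, since 0.3.2 itself calls it a correlation. The words following Pearson in 9.3 leave other statistics open, and a statistical analysis plan that is not shown may name them. Section 2.1 mentions correlation and usefulness side by side, and nowhere does the protocol say that r alone decides usefulness. All of this stands, and it limits the point to an improvement in wording. It does not remove the point: the one method the protocol does name is ill-suited to an ordered stage, and the verification purpose in 9.4 has no measure attached.

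A reader might infer several stronger things that the documents do not support:
- **That r mainly reflects case mix.** The check shows that r moves at least as much with true discrimination.
- **That Spearman or threshold AUROCs cure the dependence on mix.** In the illustration Spearman spans 0.31 (0.74 − 0.43) against 0.22 for Pearson, and the AUROC for stage ≥2 spans 0.18.
- **That the markers are skewed and every pathology scale is ordinal.** Skew is not stated anywhere, and an ordered scale is documented for fibrosis only.
- **That devices will be ranked on coefficients from different hospitals.** The third sentence of 9.3 correlates the index with another device, which already needs both measurements in the same patient. No section plans a ranking of separate coefficients. The availability rule in 5.2.6 and its neighbours matters only if such a comparison is added.

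**Conclusion.** The point holds in a limited form. Section 9.3 names Pearson's r, open-endedly, as the only statistic for the indices against pathology. For fibrosis the reference is an ordered stage, and no measure of stage separation is attached to the 100 + 20 verification cases. Under the assumed means and noise, stage mix alone moves r between 0.49 and 0.71 while stage-by-stage discrimination is unchanged at 0.78.

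Those sizes rest on assumed values, because the protocol gives no stage distribution. In the equal-step model the range due to mix is 0.29 to 0.47 for weak discrimination (d = 0.3) and 0.71 to 0.87 for strong discrimination (d = 1.0). The direction does not depend on these choices.

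It would go too far to say that the study's question cannot be answered. Pearson carries real information about the index. It is incomplete as evidence of usefulness and hard to interpret without the stage distribution.

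**What to change.** 1. In 9.3, use Spearman or Kendall for the index against fibrosis stage, and for any other graded or skewed variable. This deals with the ordinal scale and skew, not with case mix. Pearson may remain as a descriptive measure.
2. In 9.4, name the main measure of usefulness in the verification set: a pairwise-stage (Obuchowski-type) index with weights fixed in advance and a 95% CI.
3. Report threshold AUROCs as secondary, always beside the stage distribution of the verification set.
4. Give these results with and without the healthy volunteers.
5. If accuracy is compared between devices, restrict each comparison to patients measured on both.

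The cost is wording only; no data collection changes. The one real downside is in step 5, where each paired comparison will have fewer patients.

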Liver stiffness measured by Shear wave imaging such as FibroScan, VTQ, SWE, SwSm, SWE_GE is affected by inflammation, jaundice, congestion and the like besides fibrosis [10, 20-22], whereas RTE influences inflammation There are reports that it can evaluate fibrosis without receiving it [23]. Therefore, by simultaneously measuring both, there is a possibility that the extent of inflammation and fibrosis of the liver can be evaluated separately.

On the other hand, steatosis of the liver, a method to obtain it from the attenuation coefficient of ultrasonic wave has been reported in the 1980 's [24-27], FibroScan measures liver hardness and simultaneously determines attenuation coefficient of ultrasonic wave Controlled Attenuation Parameter (CAP) has been installed and its usefulness has been reported [28].

In this issue, SWM, which is Shear wave elastography, and attenuation measurement function have been developed from Hitachi Aloka Medical, Inc. and it has become possible to measure on the same equipment as RTE which is conventional Strain elastography.

Therefore, for liver disease cases subject to liver biopsy or hepatectomy, indexes of hepatic fibrosis, inflammation, fatty liver are calculated using the results of pathological diagnosis as teacher data, using the results of RTE, SWM and attenuation measurement Consider an algorithm to do. In addition, blood collection test, pathological diagnosis, FibroScan, VTQ, SWE, SwSm, SWE_GE and MR Touch are performed, their correlation is evaluated, and its usefulness is examined.

3. Target

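### A marginal correlation of the inflammation index with inflammation grade, the only method section 9.3 names, does not by itself support separate evaluation of inflammation and fibrosis

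*Protocol*

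**What the plan says.** **Rationale.** Protocol section 2.1 says that shear-wave stiffness "is affected by inflammation, jaundice, congestion and the like besides fibrosis", and cites reports that RTE reflects fibrosis without the influence of inflammation. It infers that "by simultaneously measuring both, there is a possibility that the extent of inflammation and fibrosis of the liver can be evaluated separately", and then proposes the algorithm.

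**Primary endpoint.** Section 8.1.1: "Develop algorithms to calculate indices of hepatic fibrosis, inflammation, fatty liver using RTE, SWM, and attenuation measurement". Each feature has its own index.

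**Derivation.** Under section 9.2 an "index of liver fibrosis, inflammation, fatty liver is calculated using multiple regression analysis and data mining etc", with pathology as the outcome and the imaging measures as predictors. Histological fibrosis is not named as a covariate when the inflammation index is built.

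**Check against pathology.** Section 9.3 names Pearson correlation, with the list of methods left open, to evaluate "the relevance between the indicators of hepatic fibrosis, inflammation and fattying by each elastography and attenuation measurement and the pathological diagnosis". The only further step named is by disease: "Also, sub-analysis is performed for each disease and examined". No section names a partial correlation, a model holding more than one histological feature, stratification by fibrosis stage, or a comparison of the inflammation index with fibrosis stage.

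**Data.** Section 9.4 sets aside 300 biopsy or resection cases to build the indices and 100 to verify them. Section 5.2.2 names fibrosis as the feature the pathology committee grades and does not mention inflammation or steatosis.

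**The concern.** The fibrosis and inflammation indices come from the same imaging inputs. A regression fitted to predict inflammation grade uses any signal that helps, and that includes fibrosis signal whenever the two grades go together. The result could be a fibrosis index under another name. It would still correlate with inflammation grade, because fibrosis does.

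What is at stake is how the result is read. The possibility raised in section 2.1 concerns separate evaluation. If a report gave only the correlation of the inflammation index with inflammation grade, a reader could take it as evidence that SWM combined with RTE isolates inflammation. The same number could arise with no inflammation information in the index at all.

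**Working it through.** **Inputs from the protocol.** Section 9.4: 300 + 100 = 400 pathology cases, 30 + 20 = 50 healthy volunteers, 450 in all. These sums agree with section 4.1.2. The protocol states no alpha, power or target correlation, so it has no figure of its own on this point to reproduce. The 20 healthy verification cases are left out below because the plan describes no biopsy for them.

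**Assumptions.** Two-sided alpha 0.05. Let λ be the correlation of the index with fibrosis stage, range 0.5 to 0.8. Let ρ be the correlation of fibrosis stage with inflammation grade, range 0.2 to 0.7.

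**Step 1: expected correlation.** If the index carries no inflammation information once fibrosis is known, then r(index, inflammation) = λ × ρ, and its partial correlation given fibrosis is 0.

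**Step 2: chance that it is significant.** By the Fisher z approximation this is close to Φ(atanh(r) × √(n − 3) − 1.96), plus the small opposite tail. With n = 100, √97 = 9.849. For r = 0.7 × 0.5 = 0.35: atanh(0.35) = 0.3654; 0.3654 × 9.849 = 3.599; Φ(3.599 − 1.96) = Φ(1.639) = 0.949.

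| λ | ρ | r = λρ | Significant, n = 100 |
|---|---|---|---|
| 0.5 | 0.2 | 0.10 | 17% |
| 0.7 | 0.3 | 0.21 | 56% |
| 0.6 | 0.4 | 0.24 | 67% |
| 0.7 | 0.5 | 0.35 | 95% |
| 0.8 | 0.7 | 0.56 | nearly 100% |

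**Step 3: the planned sequence, simulated.** An inflammation index was built by multiple regression on 300 cases and tested on 100, with five fibrosis stages and four inflammation grades, 2,000 runs per setting. Of the three imaging inputs, two carried fibrosis only and one was noise. This is the unfavourable case that a check should be able to expose.

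| ρ | Mean marginal r | Marginal significant | Partial (given stage) significant |
|---|---|---|---|
| 0 | 0.00 | 4% | 5% |
| 0.3 | 0.20 | 51% | 5% |
| 0.4 | 0.27 | 77% | 5% |
| 0.5 | 0.34 | 94% | 6% |
| 0.6 | 0.41 | 99% | 5% |
| 0.7 | 0.48 | 100% | 4% |

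The effect comes entirely from ρ: at ρ = 0 the marginal test keeps its nominal rate. Adjusting for stage returns it to about 5% when stage is read without error.

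**Step 4: adjustment when stage is read with error.** Section 2.1 concedes biopsy sampling error. Assume that observed stage correlates 0.85 with true fibrosis, with λ = 0.7 and ρ = 0.5. Then r(index, observed stage) = 0.7 × 0.85 = 0.595 and r(inflammation, observed stage) = 0.5 × 0.85 = 0.425. The partial correlation is (0.35 − 0.595 × 0.425) / √((1 − 0.354)(1 − 0.181)) = 0.097 / 0.727 ≈ 0.13. At n = 100 this is significant about 26% of the time. That is far below 95%, but it is not 5%.

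**The case against.** **The protocol does not claim separation.** A reader might infer that the whole study rests on it, or that a significant correlation would be declared confirmation. The text supports neither. Section 2.1 speaks of a possibility, the stated purpose is non-invasive evaluation of the liver's general condition, and no endpoint, alpha or success criterion concerns separation. This stands and limits the point to how a correlation may be read.

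**Section 9.3 does not rule out a better check.** A reader might also infer that the planned analysis cannot tell the two kinds of index apart. That goes too far. The wording is open-ended and does not tie each index to its own feature. Correlating the inflammation index with fibrosis stage fits within it, and at λ = 0.7, ρ = 0.5 would give 0.70 against fibrosis and 0.35 against inflammation, which exposes the problem. The pairwise coefficients also determine the partial one. This stands, but none of it is spelled out. An SAP not shown here may add it; the method the protocol itself names does not address the question its background raises.

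**The correlation between grades is assumed.** True. No section gives it, and section 5.1.1 lists mixed etiologies and resections for metastatic cancer, so a single value is doubtful. The low end of the range must be shown with the high end.

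**Marginal agreement is a fair measure of usefulness.** Also true, so it should stay. It answers a different question from separation.

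**Conclusion.** The point holds as a limit on interpretation. A marginal correlation between the inflammation index and inflammation grade does not by itself support separate evaluation of inflammation and fibrosis. The chance that a fibrosis-only index reaches significance in 100 verification cases runs from about 17% (0.5 × 0.2) to nearly 100% (0.8 × 0.7), and is nominal if the two grades are uncorrelated. These figures rest on the assumed λ, ρ and two-sided 0.05. The multiple regression in section 9.2 does not remove the problem, since histological fibrosis is not among its stated predictors. The documents do not show that the indices will fail to separate the two features, or that the sponsor would claim success from a marginal correlation alone.

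**What to change.** In section 9.3, for the verification set, report for each index:

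1. its correlation with all three histological grades, including the two it is not meant to measure;
2. its partial rank correlation, or ordinal-model coefficient, with its own grade adjusted for the other two, with a confidence interval;
3. alongside these, the correlations among the three indices and among the three grades.

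State that any conclusion about evaluating inflammation and fibrosis separately will rest on items 1 and 2, not on the marginal correlation with its own grade. State also that biopsy sampling error leaves residual confounding, so a small non-zero adjusted association is not proof of separation. For that reason a simple non-zero criterion should not be used as the gate.

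The cost is a little more analysis. Inflammation and steatosis grades are already needed to train the indices in the primary endpoint, but section 5.2.2 names only a fibrosis reading, so it should state that the other two features are graded and on what scale.
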